**Table 3 T3:**
[figure not shown]
Timing of assessments for mothers and babies in the ECOBABe study.

#### Maternal dietary intake

2.9.2

All women report their antenatal dietary intake using a modified version of The New Zealand Adolescent Food Frequency Questionnaire (NZAFFQ).^[48]^ The questionnaire asks respondents to rate the frequency with which they consume specific types of food and fluids. No food frequency questionnaire (FFQ) has yet been validated for pregnant women in New Zealand. While FFQs have been validated for New Zealand adults,^[49,50]^ they include questions regarding alcohol (which pregnant women are advised against consuming). Thus, we are using a modified version of the NZAFFQ, which does not include such questions. Nevertheless, potential maternal alcohol intake during pregnancy is recorded on a maternal background and medical history questionnaire (below).

#### Maternal physical activity

2.9.3

The women report their antenatal physical activity using the short form of the International Physical Activity Questionnaire (IPAQ).^[51]^ All women are asked to recall their physical activity levels for the previous seven days.

#### Maternal background, medical history, and anthropometry

2.9.4

The women complete a brief questionnaire regarding their:

demographic information: date of birth, ethnicity, place of birth, educationmedical history: serious health problems, medical treatments, family history of medical problems, previous pregnanciesprobiotic supplement intakecurrent pregnancy information: conception type, illness during pregnancy, smoking and alcohol consumption during pregnancycurrent participation in other clinical trialspre-pregnancy weight and height.

#### Neonatal assessments

2.9.5

Neonatal assessments differ according to participant study group (CS vs vaginal birth). Post-treatment neonatal clinical assessments are performed only on babies born by CS. A member of the study team records birth weight, length, head circumference, abdominal circumference, and chest circumference measurements for all CS-born babies. These measurements are taken using the weighing scales and tape measures in the hospital where participants give birth. Other neonatal clinical information is also recorded by a research clinician for CS-born babies (e.g., Apgar scores, breastfeeding initiation, and skin-to-skin start time).

Neonatal clinical information for vaginal-born babies are obtained from medical records. Note that abdominal and chest circumference measurements at birth are not recorded for vaginal-born babies as these are not standard measurements, and it is not feasible to have a member of the study team present at these births.

#### Baby anthropometry and body composition

2.9.6

At 1 and 3 months of age, all babies are weighed and measured while naked. They are weighed using an infant weighing scale. Crown-heel length is recorded three times using a neonatometer (Holtain Ltd., Crymych, UK) with gentle pressure applied to the legs to ensure the body is flat as possible. The median value of the three measurements will be used for analysis. Both the weighing scale and neonatometer are regularly calibrated. Head, abdominal, and chest circumferences are measured using disposable paper measuring tapes. At 3 months, baby body composition is assessed using DXA while wrapped in a blanket (Lunar Prodigy and Lunar iDXA, GE Medical Systems, Chicago, IL).

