### Interventions

2.3

Eligible babies in the elective CS group are randomized in a 1:1 ratio to receive either active treatment (3 ml vaginal bacteria supernatant) or placebo (3 ml sterile water). A folded 13 × 300 mm sterile gauze with an x-ray strip (Propax, New Zealand) is inserted into the lower vagina of women in the CS group and removed after approximately 30 minutes, as close as possible to their surgery. Women can choose to insert and/or remove the gauze themselves, or have these tasks performed by a clinical member of the research team. Sterile gloves are worn during insertion and removal of the gauze. A counter-signed study swab-count sticker is used to verify the removal of the swab prior to surgery, and added to the woman's clinical notes.

After removal, the gauze is vertically cut into two equal sized pieces using sterile scissors. One piece is kept on ice in a sterile container for transportation back to the Liggins Institute laboratory. The other piece is placed in a sterile syringe with 5 ml of sterile water and mixed to obtain a vaginal bacteria supernatant. Next, 3 ml of this supernatant is transferred to a 3 ml sterile syringe in preparation for oral administration to babies randomized to receive active treatment. The remaining 2 ml of supernatant are transferred to a microcentrifuge tube and stored on ice for transportation back to the laboratory, for later microbiota assessment. If a baby is randomized to receive placebo, only 3 ml of sterile water is placed in the syringe, while the prepared vaginal supernatant is reserved solely for microbiota assessment.

If the attending clinician assesses the newborn as healthy, a member of the research team uses the pre-filled syringe to orally administer either active treatment (3 ml vaginal bacteria supernatant) or placebo (3 ml sterile water). Administration occurs as soon as possible after birth (no later than one hour). Babies in the vaginal-born reference group are not randomized, as no administration of active treatment or placebo occurs in this group.

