### Outcomes

2.4

Primary outcome:

Difference in the community structure of the gut microbiota between CS groups at 1 month of age.

Secondary outcomes:

Difference in the overall gut microbiota community between CS groups at 24 hours and 3 months of age.Similarity of CS seeded and placebo gut microbiota profiles to those born vaginally at 24 hours, 1 and 3 months of age.Degree of maternal vaginal bacterial strain transfer in CS-born babies at 24 hours, 1 and 3 months of age.BMI *z*-score at 1 and 3 months of age.Total body fat percentage from whole-body dual-energy absorptiometry (DXA) at 3 months of age.

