### Sample size

2.6

We intend to randomize 30 healthy babies in the CS group on a 1:1 basis to intervention or placebo (15 per group). A power calculation indicated that 15 babies per CS group would be sufficient to detect a moderate effect size of 0.25 standard deviations for our primary outcome (power calculation for balanced one-way ANOVA test, 85% power, α = 0.05). In addition, we intend to recruit 15 babies born vaginally as a reference group.

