### Randomization, allocation, and blinding

2.8

Healthy CS-born babies are randomized in a 1:1 ratio to either treatment or placebo group, using computer-generated randomization. Mothers of randomized babies were blinded to group allocation; the researchers analyzing the primary outcome data, are blinded to baby group (active treatment, placebo, or vaginal-born reference group). For pragmatic reasons, it is not possible for the researcher administering the intervention to be blinded, as they are the only member of the research team present at a woman's CS. Participant un-blinding during the study is permissible in the case of any serious adverse events and upon recommendation by the study's independent data monitoring committee (DMC).

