#### Microbial and statistical analyses

2.9.8

Metagenomic sequencing data will be processed with bioBakery workflows using docker images available at http://huttenhower.sph.harvard.edu/biobakery_workflows. Briefly, sequence data quality control, including removal of any human reads, will be conducted using KneadData. Taxonomic and functional profiles of the microbiota will be generated using MetaPhlAn v2.6^[52]^ and HUMAnN2^[53]^ respectively. Strain-level taxonomic profiling will be achieved by SNP haplotype based profiling using StrainPhlAn software.^[54]^ The resulting SNP haplotypes will be used to identify the proportion of shared and unrelated strains between mother-baby pairs, comparing these proportions across treatment groups.

Permutational multivariate analysis of variance (PERMANOVA) will be used to identify any significant differences in the overall microbial community structure between treatment groups. Additionally, Multivariate Association with Linear Models (MaAsLin2) will be used to identify any significant associations between specific microbial taxa and treatment groups. Both taxonomic and functional profiles will be compared. Microbiota stability across time points will be assessed using Bray Curtis dissimilarity. Microbial alpha diversity will be assessed using Shannon's diversity index and gene counts.

Treatment evaluation on clinical outcomes will be performed on the basis of intention to treat, using data collected from all randomized participants. Generalized linear regression models will be used to assess treatment effects, adjusting for sex. Model-adjusted estimates and the difference among the three groups will be calculated and tested. Planned subgroup analysis by sex may be conducted on secondary outcomes to evaluate the consistency of possible treatment effects in males and females. Analyses of non-microbiome data will be performed in SAS v9.4, SPSS v26, and/or Minitab v16. Statistical tests will be two-tailed and significance maintained at 5% level.

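### Body fat percentage is measured on two DXA models but the stated model adjusts only for sex, so any offset between models can enter the group comparisons, chiefly the one with the non-randomised vaginal-born group (minor)

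*Protocol article*

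**What the plan says.** All places are in the protocol article.

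- **Outcome (Section 2.4).** One secondary outcome is "Total body fat percentage from whole-body dual-energy absorptiometry (DXA) at 3 months of age".
- **Measurement (Section 2.9.6).** At 3 months "baby body composition is assessed using DXA while wrapped in a blanket (Lunar Prodigy and Lunar iDXA". The section reports regular calibration of the weighing scale and the neonatometer. It does not say how babies are assigned to a scanner, whether one model replaced the other, or whether the two are cross-calibrated.
- **Analysis (Section 2.9.8).** For clinical outcomes, "Generalized linear regression models will be used to assess treatment effects, adjusting for sex". It continues: "Model-adjusted estimates and the difference among the three groups will be calculated and tested".
- **Groups (Sections 2.3, 2.6, 2.8).** Two groups are randomised: "Healthy CS-born babies are randomized in a 1:1 ratio to either treatment or placebo group, using computer-generated randomization", with 15 babies planned in each. The third, also planned at 15, is not: "Babies in the vaginal-born reference group are not randomized, as no administration of active treatment or placebo occurs in this group".

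**The concern.** The article introduces a measurement factor, the scanner model, and then states an adjustment set that leaves it out. If the two models give different readings for the same baby, part of the spread in body fat percentage comes from the machine.

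What follows depends on the comparison. Randomisation protects the comparison of seeded with placebo babies on average, so an offset there costs precision and may fall unevenly by chance. Nothing in the design balances the scanner mix of the vaginal-born group against that of the caesarean arms, yet Section 2.9.8 commits to testing differences among all three groups. A difference that comes from the machine could then be read as a difference by mode of birth, or as a seeded group lying closer to or further from the reference.

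**Working it through.** **Inputs.** From the article: 15 babies per group, two-sided tests at 5%, sex as the only named covariate. The article gives no SD for body fat, no target difference, no offset between scanners and no scanner mix, so there is no plan figure to reproduce. The following are assumptions: an offset δ of 0.25, 0.5 or 1.0 within-scanner SD, and the scanner shares named in each step. Comparisons are sized as two-sample t-tests of 15 versus 15, without covariates.

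**Step 1. Bias.** Bias = δ × (share on one model in group A − share on that model in group B). It is zero if δ = 0 or if the shares are equal.

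**Step 2. Randomised caesarean arms.** The scan comes after randomisation, so the expected difference in shares is zero and so is the expected bias. The offset adds variance. With share p on one model, outcome variance is multiplied by 1 + δ²p(1 − p). At p = 0.5:

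| δ (SD) | Variance multiplier | Type I error, 20,000 simulated trials |
|---|---|---|
| 0.25 | 1 + 0.0625 × 0.25 = 1.016 | about 5% |
| 0.5 | 1 + 0.25 × 0.25 = 1.0625 | about 5% |
| 1.0 | 1 + 1 × 0.25 = 1.25 | about 5% |

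Simulated type I error was 4.9% to 5.1% throughout.

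**Step 3. Chance imbalance in a single trial.** Suppose exactly 15 of the 30 caesarean babies are scanned on each model. The number in one arm on a given model is then hypergeometric, and the shares differ by an odd number of fifteenths. A 7 versus 8 split has probability 2 × 0.267 = 0.534, so:

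- P(shares differ by at least 20 points) = 1 − 0.534 = 0.466
- P(shares differ by at least 33 points) = 0.143

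If each baby is instead assigned independently with p = 0.5, the figures are about 36% and 10%. A 33-point imbalance moves that trial's estimate by 0.33δ. This is random error and is reflected in the standard error.

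**Step 4. Comparison with the vaginal-born group.** Here the shares need not be equal even in expectation.

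*Complete separation (100% versus 0%).* Bias = δ. The t statistic has 28 degrees of freedom and noncentrality δ√(15/2) = 2.739δ, that is 0.685, 1.369 and 2.739. The probability of exceeding the 5% critical value of 2.048 in absolute size when there is no true difference is 10.1%, 26.2% and 75.3%. Simulation gave 10%, 27% and 76%.

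*Partial separation (80% versus 20%).* Bias = 0.6δ = 0.15, 0.30 and 0.60 SD. Simulated type I error is about 7%, 12–13% and 31–32%.

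**Step 5. What a covariate can do.** A scanner term removes a constant offset as long as both models were used within at least one group. If all vaginal-born babies were on one model and all caesarean babies on the other, scanner and birth group coincide and no covariate can separate them.

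**The case against.** The strongest reply is that this argues from silence. Section 2.9.8 says the models adjust for sex; it does not say that nothing else may be added. Scanner assignment, cross-calibration and technical covariates are details that an article often leaves to the full protocol or analysis plan. That is fair for assignment and cross-calibration, and neither is held against the plan here. It does not dispose of the point, because the article does state an adjustment set for these outcomes, and that set does not fit the measurement it describes.

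Three stronger readings are tempting, and the documents do not support them.

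- **That the randomised comparison is biased.** Scanning follows randomisation by about three months and mothers are blinded, so nothing in the article ties scanner to arm. A shift after an unlucky split is conditional on that split and is not an expected bias. The probabilities in Step 3 also depend on an even use of the two models; they fall if few babies are scanned on one of them.
- **That the vaginal-born group is confounded with scanner.** This would need a different period or site for those babies. Sections 2.1 and 2.7 describe recruitment of both groups together, most follow-up at one research unit, and off-site visits only at one month. Confounding is possible but nothing indicates it.
- **That the shift would rival the differences of interest.** The article gives no target difference, SD or offset for body fat, so no such comparison can be made.

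The reply is also right about weight. The objectives in Section 1.2 concern the gut microbiota, and body fat is one secondary outcome.

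**Conclusion.** The point holds as a minor one. Two scanner models feed one secondary outcome, and the only stated adjustment is for sex, so an offset between models can enter the comparisons; the documents do not show that it does.

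For the randomised arms, the consequence is a variance increase of 1.6% to 25% across the assumed offsets with even scanner use, with type I error unchanged at about 5%. For the test against the vaginal-born group, systematic bias arises only if both conditions hold: unequal scanner mix and different readings. In the extreme case of complete separation, type I error is about 10% to 75% for offsets of 0.25 to 1.0 SD. If the scanners are cross-calibrated without residual offset, or used equally across groups, the bias is zero.

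**What to change.** 1. Record the scanner model for each baby's 3-month scan.
2. Add scanner model as a fixed covariate, alongside sex, in the body-fat model.
3. Report the scanner mix by group.
4. If the vaginal-born babies were all scanned on a model not used for the caesarean babies, report their body fat descriptively and do not test it against the other groups.

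The cost is one degree of freedom. With 45 babies, three groups and sex, residual degrees of freedom fall from 45 − 4 = 41 to 40.

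Moving all remaining scans to one model is not recommended as a general rule. One machine may no longer be available, and if the babies still to be scanned come mostly from one group, the change would create the separation it is meant to avoid.

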#### Sample collection and processing

2.9.7

Baby stool samples are collected by the parents from fresh nappies within the first 24 hours of life, and again at 1 and 3 months of age. Approximately one gram of stool is collected using the scoop attached to the lid of a sterile specimen tube (Sarstedt, Nümbrecht, Germany, Catalogue #SARS80.623). The tubes are prefilled with 5 ml of DNA/RNA Shield^TM^ solution (Zymo Research, Irvine, California, US, Catalogue #R1100) enabling them to be kept stable at room temperature until transfer to the laboratory. Parents are asked to shake the tightly-closed tube to mix the stool with the solution immediately after collection. Parents record the date and time of sample collection on an accompanying collection card. Upon arrival at the laboratory, stool samples are split into 1 ml aliquots and stored at −80°C.

Maternal vaginal microbiota samples (2 ml of vaginal bacteria supernatant and the remaining half of the gauze swab) are collected from all mothers in the CS group just prior to their scheduled CS, and are kept on ice until transfer to −80°C.

Microbial DNA will be extracted using the ZymoBIOMICS^TM^ 96 MagBead DNA kit (Catalogue #D4308) according to the manufacturer's instructions. A blank DNA extraction control consisting of 1 ml of sterile water will be run in parallel for contamination testing. In addition, the ZymoBIOMICS^TM^ microbial community standard (Catalogue #D6300) will serve as an extraction bias control. DNA extracts will be quantified using the Qubit^TM^ dsDNA High Sensitivity Assay kit (Catalogue #Q32851) with a Qubit^TM^ 3.0 fluorometer. Whole metagenome shotgun sequencing will be performed by an independent accredited commercial provider.

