#### Timing of assessments

2.9.1

Babies are assessed at three time-points over the course of the study: birth (24 hours), 1 month, and 3 months (Table 3). All mothers are assessed for eligibility in the antenatal period, with just postnatal maternal health issues recorded thereafter (Table 3). Mothers are reminded of their study visits via email or text message. Fuel vouchers and free parking are provided for all study visits, and taxis are booked for mothers who are unable to drive to appointments. Study visits are rescheduled if a mother indicates that she will be unable to attend at the booked time.

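### The 24-hour microbiome outcomes accept any stool from birth to 24 hours, with no minimum interval after dosing and no use of the recorded collection time

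*Protocol article*

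**What the plan says.** The Outcomes section (2.4) lists three secondary microbiome outcomes with a 24-hour time point:

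- "Difference in the overall gut microbiota community between CS groups at 24 hours and 3 months of age"
- "Similarity of CS seeded and placebo gut microbiota profiles to those born vaginally at 24 hours, 1 and 3 months of age"
- "Degree of maternal vaginal bacterial strain transfer in CS-born babies at 24 hours, 1 and 3 months of age"

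Sample collection and processing (2.9.7) defines the stool that supplies them: "Baby stool samples are collected by the parents from fresh nappies within the first 24 hours of life, and again at 1 and 3 months". It adds that "Parents record the date and time of sample collection on an accompanying collection card". Timing of assessments (2.9.1) names the time point as follows: "Babies are assessed at three time-points over the course of the study: birth (24 hours), 1 month, and 3 months".

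On dosing, Interventions (2.3) says: "Administration occurs as soon as possible after birth (no later than one hour").

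Microbial and statistical analyses (2.9.8) names PERMANOVA, MaAsLin2 and strain-sharing proportions for the microbiome data. It mentions neither hours since dosing nor age at collection. The only adjustment variable in that section is sex, in the regression models for treatment effects.

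**The concern.** The dose goes in by mouth and the outcome is read from stool, so a sample is informative about seeding only if it was passed after the dose could have reached it. The sampling rule has an upper limit but no lower one. A parent who follows it exactly can hand in a stool passed before the dose or minutes after it, and that sample enters the 24-hour analysis on the same footing as one passed at 23 hours.

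Two things are at stake. Between the CS arms, unexposed samples in the seeded group resemble placebo samples and pull the 24-hour difference and the strain-transfer estimate towards zero. This is the sample closest to dosing, so a diluted result could be misread as failed delivery by a route that has not been tested before. In the comparison with vaginal-born babies there is a second problem. Those babies meet maternal bacteria during birth, are not randomized, and have no study team member at the birth. If their stools are collected at a different age from those of the CS babies, age is mixed with birth mode.

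**Working it through.** The article gives no figure to reproduce here; the sample-size statement (2.6) concerns the 1-month primary outcome only. The check sets the sections side by side and then asks how much of the window can be affected.

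**Inputs from the article**
- Stool window: 0 to 24 hours of life (2.9.7).
- Latest dosing time: 1 hour after birth (2.3).
- Seeded arm: 15 babies (2.6).
- Time from mouth to stool: not given.

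**Step 1. What is certainly unexposed.** Stool passed before dosing can fall only in the first hour. With collection times evenly spread (assumption) and dosing always at the limit (assumption, the least favourable case), the share is 1/24 = 0.042, or about 4%. In 15 seeded babies that is 15 × 1/24 = 0.6 expected samples. The chance that at least one of the 15 is affected is 1 − (23/24)^15 = 0.47. Earlier dosing lowers these figures. A collection pattern concentrated in the first hour would raise them, and one concentrated later would lower them.

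**Step 2. What may also be uninformative.** If the dose needs a lag of L hours to appear in stool, the share under the same assumptions is (1 + L)/24. The values of L are assumptions that show the range only:

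| L (hours) | Share of window | Expected of 15 seeded |
|---|---|---|
| 0 | 1/24 = 4% | 0.6 |
| 3 | 4/24 = 17% | 2.5 |
| 6 | 7/24 = 29% | 4.4 |
| 12 | 13/24 = 54% | 8.1 |

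Only the first row rests on the article's own times. The spread of the others shows that the total cannot be pinned down.

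**Step 3. Direction of the effect.** For a simple difference in means, if a share q of seeded samples look like placebo samples, the expected difference is multiplied by (1 − q). At q = 1/24 that is 0.96. The same direction is expected for PERMANOVA and for strain-sharing proportions, but this factor is not derived for them.

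**Step 4. Would a time covariate repair it?** Not between the CS arms. A main effect of hours shifts both arms alike and leaves one treatment effect averaged over early and late samples, so the dilution stays. A treatment-by-time term, or restriction to later samples, is needed. For the comparison with vaginal-born babies the problem is a possible imbalance in age, and there age at collection as a covariate is the right tool.

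**The case against.** The best defence is that 24 hours is a nominal label. The assessment section calls the time point birth (24 hours) and the sampling section describes a window ending at 24 hours, so the sections can be read together. That stands: a reader might infer an outright contradiction, and the text does not support one. The difficulty is that the window, as stated, includes time before the exposure.

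The timing table, the flow figure, the parents' instructions and the collection card are not shown and could narrow the window. That also stands as a caution, though nothing readable does so.

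Covariates and sensitivity analyses are commonly left to a statistical analysis plan, which is not at hand. So the lack of an adjustment is not in itself the fault. The stated sampling rule is, because an analysis plan cannot create a later stool that parents were not asked to collect. The recorded times do, however, allow much of the problem to be handled afterwards.

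Pre-dose samples are probably uncommon: dosing takes place in theatre shortly after birth, and parents collect from nappies. Randomization should also balance stool timing between the CS arms. Both points limit the size. Balance does not remove dilution, and it gives no protection to the vaginal-born comparison.

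**Conclusion.** The point holds for the three 24-hour secondary outcomes. The sampling rule lets pre-dose and very early post-dose stool count as a 24-hour treatment result, and the article states no use for the collection time that would separate them.

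The part that is certain is small: at most about 4% of an evenly spread window, or 0.6 of 15 seeded samples. The rest depends on transit time, which the article does not give. A reader might infer from the longer assumed lags that a large share of samples cannot carry the dose, or that the trial would need several times as many babies. The documents support neither. The lags are assumptions, no 24-hour outcome has a stated power calculation to inflate, and the usual inflation for a mean difference is not derived for PERMANOVA or strain sharing.

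Confounding by stool age in the vaginal-born comparison is possible; nothing in the article shows that collection ages differ. The 1-month primary outcome is untouched. This is worth correcting because the remedy is cheap, but it does not threaten the trial's main result.

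**What to change.** 1. Do not count a stool collected before dosing as a 24-hour outcome. Apply this rule identically in both CS arms.
2. Report the distribution of hours from dosing to collection in the CS arms, and of age in hours at collection in all three groups.
3. Include age at collection in the 24-hour comparison with vaginal-born babies.
4. For the CS arms, keep the analysis unadjusted for stool timing and put a sensitivity analysis beside it: either restricted to samples beyond a post-dose cut-off fixed before unblinding, or with a treatment-by-time term. Stool timing arises after randomization, so this should support the unadjusted result, not replace it.
5. If collection is still open, ask parents to sample a later stool within the 24-hour window where there is more than one.

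If collection is complete, items 1 to 4 still apply. They need the collection time, which is recorded, and the dosing time. The article does not say that dosing time is recorded, but the safety check about 30 minutes after administration suggests it is known.

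The cost is slightly fewer usable 24-hour samples in groups of 15 and, under item 5, possibly a second collection tube for some babies. A treatment-by-time term will be imprecise at this sample size.
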